### Sample size and justification

Sample size calculations were based on the ability to detect increases in vegetable consumption of at least 0.5 serves per day (in Australia, a standard serve is equivalent to 75 grams vegetables or 150 grams fruit). There is evidence that this increase is feasible; for example, a review of the literature on fruit and vegetable intervention studies^7^ found an average increase of 0.6 serves of fruit and vegetables per day across studies. Even small population increases in fruit and vegetable consumption such as this are meaningful. For example, an increase of 80 g per day of fruit and vegetables has been estimated to reduce the risk of ischaemic heart disease by 10%, ischaemic stroke by 6%, lung cancer by 4% and oesophageal cancer by 6%
[22].

Of the outcome variables (fruit and vegetable consumption), it was estimated that the most challenging behaviour to shift would be vegetable consumption, therefore sample size estimates have been based on this outcome. At the time of study design, there were no recent national nutrition data in Australia (with the last national survey conducted over 12 years ago), so these estimates were based on more recent data collected in a large community-based survey of over 1500 women
[2]. In that study, women of low SEP reported mean intakes of 1.9 serves of vegetables per day (0.5 serves fewer than those of higher position), with a standard deviation of 1.1. Therefore, to detect an increase of 0.5 serves of vegetables, using the following formula to calculate the sample size for a continuous measure:

N per group = 2 * SD2 * (Zsign + Zpower)2 / delta2 , where SD = 1.1; delta = 0.5; Zsign for 5% type 1 error is 1.96 and Zpower for 20% type 2 error is 0.84, N per group = 76, totalling 152. Inflating our estimate to adjust for attrition/loss to follow-up (conservatively estimated at around 10% at each measurement point), and to account for potential design effects based on sampling within catchment areas (conservatively estimated at 1.1 or an inflation of 10%), our minimum total sample size is 152/0.70 * 1.1 = 240 (120 in each group). A sample of this size is also sufficient to examine mediation effects of at least medium size using the MacKinnon approach
[23].

### Randomisation and blinding

Women were asked to complete baseline survey measures prior to randomised group allocation. The statistician created a randomisation sequence using Stata 11.1 (StataCorp, College Station, TX) statistical software, allocating participants to either the intervention or control group in a 1:1 allocation, using random block sizes of 2 and 4. The randomisation schedule was saved in a Microsoft Excel worksheet, which was accessible only by the research fellows responsible for the group allocation of sequential participants, during the allocation period. Except for the statistician and interventionists (dietitians and research fellows administering the intervention), investigators and other staff were kept blind to the allocation of participants. Intervention staff and dietitians who delivered the intervention did not take outcome measurements or analyse data.

### Statistical methods

Descriptive statistics will be used to examine characteristics of the trial participants. Outcomes will be analysed on an intention-to-treat basis using Generalized Estimating Equations to fit regression models describing intervention effects on outcome and mediator variables. Potential confounders (e.g., age, education, country of birth, relationship status, employment status, household income, household composition) will be controlled for as necessary. Mediation analyses will be undertaken using the MacKinnon method
[23]. Content and thematic analysis will be used to analyse the qualitative process evaluation data.

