### Recruitment source

Participants were recruited from two catchment areas selected randomly from all neighbourhoods that were within 25km of Deakin University in Melbourne, Australia; were socioeconomically disadvantaged (i.e. being in the lowest quartile of disadvantage according to the Australian Bureau of Statistics Socioeconomic Index for Areas
[15]; and that had a Coles supermarket within the neighbourhood.

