### Measures

Outcome data were collected from both intervention and control participants pre- and immediately post intervention and at 6 months following the completion of the intervention. Economic data were collected alongside the outcome data from Coles electronic sales data and participants’ self-reported postal questionnaires. Additional data on the resources used to provide the intervention were collected from records kept by project staff. Process evaluation data were collected from intervention participants immediately post-intervention and also after the supermarket tour for those completing this activity.

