### Outcome variables

The primary outcome variables are vegetable purchasing and consumption. Measures of food purchasing were obtained using electronic sales data provided by Coles for consenting participants via their Flybuys cards, which participants were asked to scan each time they shopped at Coles. Individualized electronic purchasing data for each participant were collected for a 3-month period prior to intervention (retrospectively following consent), and continually during the 6-month intervention and the 6-month follow-up. Participants’ purchasing data, identified by their unique Flybuys card number, were provided in tab-delimited files and uploaded to a SQL database. The files included a unique product code; product descriptor; amount/quantity purchased; and the related expenses. For each participant, all fresh, frozen, dried and tinned vegetable items purchased were identified by product codes and the quantities (by weight) and the total expenses per each item ($).

All other primary and secondary outcomes were assessed by self-report surveys. Vegetable consumption was assessed via two measures. Firstly, respondents were asked ‘About how many serves of vegetables do you usually eat per day? (1 serve = ½ cup cooked vegetables or 1 cup salad vegetables)’ Eight response options ranged from I don’t eat vegetables, to 6 or more serves per day. This item was adapted from the 1995 National Nutrition Survey
[21], where it was shown to adequately discriminate between groups with different vegetable intakes assessed by 24-hour recall. Secondly, respondents were administered a Food Frequency Questionnaire
[21], including 21 items assessing the average consumption of commonly-consumed vegetables in the past 6 months, with nine response options ranging from never or less than once/month, to 6 or more times per day.

Secondary outcomes are fruit purchasing and consumption, assessed in the same way as vegetable purchasing/consumption. Frequency of consumption of energy-dense, nutrient poor foods and beverages were measured by the survey as a marker of unintended consequences (for example, increases in intakes of confectionery or sugar-sweetened beverages). Food security was assessed as a potential consequence of the intervention (‘In the last 12 months, were there any times that you ran out of food, and couldn’t afford to buy more?’)

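### Covariate adjustment depends on an unstated judgement of need and does not commit to the baseline outcome, so the covariate set may be chosen after the data are seen and precision may be lost

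*Protocol article*

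**What the plan says.** The analysis is set out in two sentences under Statistical methods in the protocol article. The first plans an intention-to-treat analysis by GEE regression for the outcomes and the mediators. The second gives the covariate rule: "Potential confounders (e.g., age, education, country of birth, relationship status, employment status, household income, household composition) will be controlled for as necessary". The list is introduced as examples, all seven are sociodemographic, and no criterion is given for when control is needed.

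The baseline outcome is available. According to the Measures section, both arms were assessed "pre- and immediately post intervention and at 6 months following the completion of the intervention". Under Randomisation and blinding: "Women were asked to complete baseline survey measures prior to randomised group allocation". Under Outcome variables, supermarket sales data cover the three months before the intervention. The article does not say whether baseline enters the GEE as a covariate, as one of the repeated responses, or not at all.

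Randomisation and blinding also describes 1:1 individual allocation, and it lists the statistician with the intervention staff as exceptions to blinding.

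**The concern.** Under randomisation, any baseline imbalance between arms is due to chance. Covariates then serve mainly to improve precision, and the set should be fixed without reference to the outcome results. A rule that adjusts for confounders when it seems necessary works the other way round. It invites a choice made after imbalance, or the treatment estimate, has been seen. The rule covers every outcome and mediator model, so the same freedom recurs across vegetable purchasing, two measures of vegetable consumption and the secondary outcomes.

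The pre-intervention value of the same outcome is usually its strongest predictor. The trial collects it, yet the rule does not commit to using it. Two things are at stake: whether the reported effect depends on a discretionary choice of model, and how much precision is obtained from data already in hand.

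**Working it through.** **Inputs from Sample size and justification:** difference 0.5 serves/day; SD 1.1 (from a cross-sectional survey); "Zsign for 5% type 1 error is 1.96 and Zpower for 20% type 2 error is 0.84"; division by 0.70 for attrition; design effect 1.1.

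**Assumption:** the correlation rho between baseline and follow-up is not in the article. Values of 0.3, 0.5 and 0.7 are used, with equal variance at the two times and a single follow-up contrast.

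**1. The plan's own figure.** N per group = 2 × 1.1² × (1.96 + 0.84)² / 0.5² = 75.9, so 76 per group and 152 in total. After inflation, 152 / 0.70 × 1.1 = 238.9, which the article gives as 240 (120 per arm). Both figures reproduce.

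**2. Effective size.** 120 × 0.70 = 84 analysable women per arm, and 84 / 1.1 = 76.4. The 76 used below is therefore an effective size; the headcount is about 84 per arm.

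**3. Power.** With n = 76, power = Φ(0.5 / (S × √(2/76)) − 1.96), where S is the SD that applies to the analysis:
- follow-up only: S = 1.1
- adjusted for baseline: S = 1.1 × √(1 − rho²)
- unconstrained change from baseline: S = 1.1 × √(2(1 − rho))

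For follow-up only, 0.5 / (1.1 × 0.1622) = 2.802, and Φ(2.802 − 1.96) = 0.800.

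| Assumed rho | Variance factor, baseline-adjusted | Power | Variance factor, change | Power | Variance ratio, change to adjusted |
|---|---|---|---|---|---|
| 0.3 | 0.91 | 0.836 | 1.40 | 0.658 | 1.54 |
| 0.5 | 0.75 | 0.899 | 1.00 | 0.800 | 1.33 |
| 0.7 | 0.51 | 0.975 | 0.60 | 0.951 | 1.18 |

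Baseline adjustment never does worse than the other two. The unconstrained change falls below the planned 80% when rho is below 0.5, because 2(1 − rho) then exceeds 1.

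**4. Free choice of covariates.** A null simulation used 76 per arm, 4,000 runs per setting and seven independent covariates, each explaining 0% or 2% of the variance, with rho 0.5 or 0.6. One pre-specified model, with baseline and all seven covariates, rejected in 0.046 to 0.048 of runs. Taking the most favourable of nine models (unadjusted, all seven, each singly) gave 0.064 to 0.083. Adding two models that include baseline (baseline alone; baseline with all seven) gave 0.087 to 0.123. This is a worst case under assumed covariate strengths. It shows what an unrestricted choice could do and does not estimate what will happen in this trial.

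**The case against.** The strongest reply is that the point argues from silence. The list is only of examples, a GEE over three assessments may already carry baseline as a repeated response, and a separate analysis plan may fix both matters. Much of this stands. A reader might infer that the plan excludes the baseline outcome and so certainly loses precision. The article does not support that, because the role of baseline is left open. If the repeated-measures model gives both arms a common baseline mean, it is about as efficient as baseline adjustment, and the change-score penalty does not arise.

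A reader might also infer that the trial is underpowered. It is not on this account: the sample size uses the unadjusted SD with no baseline correlation, so an unadjusted follow-up comparison keeps its 80%. Nor is there a shown gain from adding catchment area. Women are randomised individually, the sample size already carries a design effect for area, and the open list does not rule the term out.

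Finally, the article does not say who will fit the models. It bars intervention staff from analysing data and exempts the statistician from blinding. An unblinded covariate choice is therefore possible, but it is not stated to be planned.

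What the reply does not remove is the rule itself. Making adjustment conditional on need is a stated method, not an omitted detail, and an analysis plan that fixed the covariates would have to depart from it.

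**Conclusion.** The point holds in a conditional form. The covariate rule permits a choice made after the data are seen, in a trial whose statistician is not blind, and it does not commit to the one covariate most likely to matter. The possible gain from committing to baseline is modest to substantial: from 80% to about 84%, 90% or 97.5% power at an assumed correlation of 0.3, 0.5 or 0.7, measured against a comparison that ignores baseline. If the intended analysis is an unconstrained change from baseline, its power is about 66%, 80% or 95% on the same assumptions. If it already uses a common baseline mean, little precision is lost and only the open covariate choice remains. All of these figures rest on a correlation that the article does not give and on an effective 76 per arm. The change is worth making because it is cheap; the documents do not show that the planned power fails or that the type I error will be inflated.

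**What to change.** Replace the covariate sentence with one primary model per outcome, for example:

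*For each outcome, the primary analysis is a GEE of the post-intervention and 6-month values, adjusted for the baseline value of that outcome. Any further covariates form a short list fixed before outcome data are examined, and are used regardless of observed imbalance. Models with other covariate sets are sensitivity analyses.*

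A repeated-measures model with a common baseline mean across arms is an equivalent alternative. The text should say which is used, so that baseline is not both a response and a covariate in the same model. The cut-off should be examination of outcome data rather than unblinding, since the statistician is not blind. A catchment-area term is optional.

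The cost is a few sentences in the analysis section. No new data are needed and the sample size does not change.

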## Discussion

The randomised controlled trial of the ShopSmart intervention described in this protocol paper will provide much-needed data on the effects of skills-based intervention approaches for increasing fruit and vegetable consumption amongst a target group at high-risk of inadequate intakes – women of low SEP. This evidence is required in order to form appropriate policy and program responses to the epidemic of obesity and poor nutrition currently facing Australia and other countries globally. If shown to be effective, the approach could be rolled out into scalable skills-based programs that could be mail-, telephone-or web/internet-delivered at relatively low-cost, potentially implemented by governments or health care providers.

The links with Coles supermarkets and the Heart Foundation forged within this project represent rare and invaluable opportunities to work collaboratively to promote healthy eating in partnership with a major national industry player in the grocery retail market, and with a key national NGO committed to improving the eating behaviours and heart health of Australians, particularly those experiencing socioeconomic disadvantage. Other strengths of the study include the strong theoretical basis; application of an intervention mapping approach; use of objectively-assessed purchasing (sales) data; and inclusion of an evaluation of cost-effectiveness, and of unintended consequences.

Recently, a literature review examined whether nutrition interventions are more likely to be effective amongst high- than low-socioeconomic groups
[24]. That review found that nutrition interventions were less successful amongst the most socioeconomically disadvantaged participants, potentially leading to a widening of dietary and thus health inequalities. Hence interventions such as ShopSmart 4 Health that focus specifically on addressing the nutrition-related needs of those experiencing socioeconomic disadvantage are urgently required in order to redress inequalities in nutrition and associated health outcomes.

## Abbreviations

READI: Resilience for Eating and Activity Despite Inequality; SEP: Socioeconomic position; SEIFA: Socioeconomic Index for Areas.
